### Participants and sample size

A power analysis was a priory determined using the G*Power software.^38^ Based on previous studies with similar design, we expected to find nearly two times as high odds of injury occurrence in athletes during a period of high academic stress compared with low academic stress (OR=1.78; effect size (ES)=0.14)^25^ with power of 0.90 and α=0.05, two-tailed, which calculated an initial sample size of 134 participants. As in sports practice, the athlete drop-out is to be expected (due to travelling, international transfer to another club/state, etc); we adjusted the originally calculated sample size by following formula: N1=n/(1−d),^39^ where N1 is adjusted sample size, n is the sample size required as per the proposed formula (N=134) and d is the drop-out rate (d=0.10). This resulted in total sample size of 149 athletes. Inclusion criteria will be as follows: DC and non-DC registered male handball players who are competing in the first Slovenian handball league and are above 18 years of age.

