#### Blood biomarkers

There will be three to five measurement timepoints for biomarker sampling, according to the training (preparatory period, competitive period, off-season period) cycle. The athletes will be tested under similar conditions every time, after a rest day (refrainment from intensive training the day before blood collection), between 7:00 and 10:00 in the morning.

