### Statistical analysis

Statistical analysis will be performed using standard statistical software (SPSS V.27.0, IBM, Armonk, New York). Descriptive statistics will be used for all variables. Normality of data distribution will be assessed using the Shapiro-Wilk test. In case of non-normally distributed data, non-parametric statistics will be used, otherwise, the statistics for normally distributed data will be used. The data will be analysed using a logistic regression model to properly account for the dependency induced by the repeated observations over time within each subject. Main effect of all dependent variables on injury/illness occurrence will be studied using repeated measures analysis of variance (ANOVA) with time (preparation period vs competition period vs off-season period) as within factor, while group (injured/ill vs healthy) as between factor. Where significant effects will be found for group, time effects or two-way interactions, pairwise comparisons will be used to address the significant differences for each variable independently. For comparison of the groups, we will use independent t-test. The magnitude of effect for all dependent variables will be reported as partial eta squared (η^2^). In addition, *Cohens’ d* (ES) will be used to assess magnitude of difference between groups. Furthermore, regression analysis will be used to assess predictive power of individual parameters to identify injury/illness occurrence. For the correlation of subjective measures of stress with the objective measures, bivariate correlation will be used. Additionally, Bland-Altmann analysis will be used (low/high stress normative values) as previously recommended.^42^ Furthermore, receiver operating characteristic (ROC) curve analysis will be used for defining the cut-off values. Hypotheses will be accepted or rejected at p≤0.05.

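### The three-period repeated-measures ANOVA drops, variable by variable, any player with no value in one period; the drop-out allowance protects how many are analysed, not who is analysed

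*Protocol article*

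**What the plan says.** The Statistical analysis section assigns the effect of all the measured variables on injury/illness to a "repeated measures analysis of variance (ANOVA) with time (preparation period vs competition period vs off-season period) as within factor". Players are also split by health status, which enters as the second factor: "while group (injured/ill vs healthy) as between factor". The software is fixed: "Statistical analysis will be performed using standard statistical software (SPSS V.27.0, IBM, Armonk, New York". Effects from this analysis are to be reported as partial eta squared.

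The same section separately names a "logistic regression model to properly account for the dependency induced by the repeated observations over time within each subject", as well as regression, correlation, Bland-Altman and ROC analyses.

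Missing players are foreseen under Participants and sample size: "the athlete drop-out is to be expected (due to travelling, international transfer to another club/state, etc". The response there is numerical: "d is the drop-out rate (d=0.10", which takes 134 to 149. The Ethics and dissemination section lets players withdraw without giving a reason.

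On biomarkers, the Blood biomarkers section states: "There will be three to five measurement timepoints for biomarker sampling", arranged by training period. Nothing in the article says how a player with an empty period enters the ANOVA.

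**The concern.** A classical repeated-measures ANOVA works on complete rows. If a player has no value at one level of the time factor, the procedure discards him for that variable, including the values he did supply. The article does not state this deletion. It follows from the method the article names, so it is not a detail that can simply be left to a fuller analysis plan.

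The article expects some players to be lost, and its only answer is a larger enrolment target. That replaces lost numbers but does nothing about selection. The grouping factor here is injury/illness, and the outcomes include load, stress and stress-related biomarkers. If leaving the club or missing a draw is related to any of these, the remaining players differ from those enrolled, and the group and period contrasts can shift. Biomarkers carry the secondary aim and are most at risk, because each period may hold a single draw, whereas weekly reports give many chances to contribute a value.

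**Working it through.** **1. The plan's own figure.** Participants and sample size gives n = 134 and d = 0.10. N1 = n/(1 − d) = 134/0.90 = 148.9, rounded up to 149. The figure reproduces.

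**2. Numbers at the planned drop-out.** If the 10% who leave have no value in at least one period:
- 149 × 0.90 = 134.1, so 134 are analysed and 15 discarded.
- With the 200 players named in the abstract: 200 × 0.90 = 180 analysed and 20 discarded.

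The loss of numbers at the planned rate is therefore already budgeted.

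**3. Biomarkers.** Take one draw in each of three periods. Attendance a per draw among players still in the study is not given in the article. It is assumed here to be 95%, 90% or 85%, independent between draws. Complete players = N × 0.90 × a³.

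| a | a³ | of 149 | share | of 200 |
|---|---|---|---|---|
| 0.95 | 0.857 | 115 | 77% | 154 |
| 0.90 | 0.729 | 98 | 66% | 131 |
| 0.85 | 0.614 | 82 | 55% | 111 |

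If the 10% drop-out is not stacked on top, 149 × a³ gives 128, 109 and 92.

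**4. Bias from selection (illustrative simulation; all settings assumed).** Two equal groups, SD 1, within-player correlation 0.5, true group difference 0.5 SD in each period, and departure before period 3. The log-odds of leaving rise by 0, 1 or 2 per SD of the player's mean over periods 1 and 2. Group differences in periods 1, 2 and 3:

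| Loss | Slope | All players | Complete players | Mean attenuation |
|---|---|---|---|---|
| 10% | 0 | 0.494, 0.491, 0.490 | 0.492, 0.491, 0.491 | 0.1% |
| 10% | 1 | 0.502, 0.499, 0.501 | 0.475, 0.473, 0.482 | 5% |
| 10% | 2 | 0.491, 0.496, 0.493 | 0.420, 0.429, 0.448 | 12% |
| 20% | 0 | 0.500, 0.496, 0.497 | 0.494, 0.492, 0.495 | 0.8% |
| 20% | 1 | 0.491, 0.489, 0.499 | 0.447, 0.449, 0.469 | 8% |
| 20% | 2 | 0.504, 0.505, 0.506 | 0.392, 0.397, 0.432 | 19% |

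Mean attenuation is 1 minus the ratio of the three-period sums; for 10% and slope 1, 1 − 1.430/1.502 = 4.8%. The slope-0 rows show only simulation noise.

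The period contrast also moves, because the mean of the complete players shifts unequally across periods. At 10% loss and slope 1, the shift is −0.076 SD in period 1 and −0.052 in period 3, so period 3 minus period 1 is off by 0.024 SD. At 20% loss and slope 2 it is −0.158 − (−0.226) = 0.068 SD.

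**5. A second set of assumptions.** True difference 0.30, 10% loss, correlation 0.5 or 0.7. With log-odds of 0.5 to 1 per SD of earlier stress and no group effect on leaving, the complete-case estimate is 0.28 to 0.30. Log-odds of 1 for stress and a further 1 for being injured/ill give 0.25 or 0.23, that is, 17% or 23% too small.

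**The case against.** Much can be said for the plan, and several points stand.

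- **Scope.** A reader might infer that leavers' data are lost to the whole study, so that all results describe only those who lasted the season. The article does not support that. Deletion affects this one ANOVA, separately for each variable. The logistic model for repeated observations, the regression, the correlations and the ROC analysis do not need three complete periods.
- **Weekly measures.** If weekly reports are averaged within a period, a player who leaves part-way through the last period still has a value there and is kept. Only a wholly empty period removes him.
- **Numbers.** The planned 10% loss is covered by the inflation to 149, and more comfortably by the 200 in the abstract. What remains is selection, plus any draws missed beyond that 10%.
- **Injured players and blood draws.** It is tempting to assume that sidelined players will miss sampling. The Blood biomarkers section does not say so. It asks for a rest day beforehand and a morning visit, and a sidelined player can meet the first easily.
- **Five draws.** Requiring all five draws would give lower complete-case counts, but that needs a five-level time factor. The ANOVA has three levels, and a period mean can absorb a missed draw.
- **Informative departure is conjecture.** The causes the article names are travel and transfer. If these are unrelated to the outcomes, there is no bias.
- **A fuller plan.** An unseen analysis plan could impute before the ANOVA, and the article does not exclude this.

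The last point does not remove the fault. As published, the article names a method that deletes incomplete players, expects incomplete players, and offers only a larger sample in response.

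**Conclusion.** The point holds for the three-period ANOVA alone. At the plan's own drop-out rate, up to 15 of 149 players (20 of 200) are removed from a variable's analysis even where they supplied one or two periods, and the inflation to 149 does not address who these players are. Biomarkers could lose considerably more: about 115, 98 or 82 of 149 would be complete under the assumed attendance rates.

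That deletion occurs is close to certain, because it is a property of the named method. The size of any bias is not. It is essentially nil if departure is random, and runs from a few per cent to about 20% attenuation of the group difference in the illustrative scenarios. The upper end needs either a steep dependence on earlier values with 20% loss, or an added effect of being injured/ill on leaving. The article gives no figure that would decide between these, so a bias near 20% should not be read as a prediction. The change is worth making because a better method is available at almost no cost.

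**What to change.** In the Statistical analysis section, replace the repeated-measures ANOVA with a linear mixed model (SPSS MIXED):

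- **Terms:** period, group and group-by-period as fixed effects, and player as a random effect. The group terms are essential, since they are the contrasts the section sets out to test.
- **Data:** every available period or timepoint from every enrolled player, including those who later leave. This remains valid when departure depends on values already observed and modelled, but not when it depends on unobserved ones.
- **Group:** define it so that it does not depend on length of follow-up, for example as health-problem status within each period. Otherwise early leavers are labelled healthy by default. With an assumed constant hazard giving 50% injured/ill over 46 weeks, only 1 − 0.5^(20/46) = 26% would carry that label by week 20.
- **Reporting:** keep the complete-case ANOVA as a sensitivity analysis and give the number of players contributing to each period. If the two analyses use different group definitions, also refit the mixed model on complete players only, so that the effect of selection can be seen on its own.

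The cost is analysis wording and slightly more analysis work; no new data, visits or software are needed. Partial eta squared gives way to model-based mean differences with confidence intervals. Within-period status also asks a somewhat different question from a season-long label, and the text should say so.

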### Biomarkers

Biomarker discovery and validation is a critical aim of the medical and scientific community.^33^ Biomarkers can be used as an objective assessment tool for health, performance, recovery and talent identification in elite sport. Among the most critical hormones for athletes seem to be cortisol, testosterone, dehydroepiandrosterone and immunoglobulin-A (Ig-A). However, testosterone to cortisol (T:C) ratio is considered to be more sensitive to training stress than either measure alone,^33^ as several studies report poor performance outcomes and suboptimal training adaptations in athletes with a low T:C ratio.^34 35^ However, to the best of the authors’ knowledge, no previous work has examined the use of biomarkers for injury prevention, recovery after an injury or identification of individuals at increased risk.

Given all of the above, there is a need for better health surveillance, load monitoring and support services with an emphasis on injury/illness prevention and rehabilitation.^36^ As DC athletes have a wider variety of loads that pose greater psychophysiological strain to them, they could also be at an increased risk for injury/illness. Therefore, more comprehensive monitoring of potential risk factors in this specific population is warranted. It is not yet known, but important to determine how much of overall load can an athlete withstand before injury/illness occurs. Thus, the primary aim of this study is to determine how specific physical, psychosocial and DC loads affect the occurrence of injuries and illnesses in elite handball players and how much of a variation in the athlete’s load leads to an occurrence of an injury/illness. A secondary aim is to determine the association between objective and subjective measures of stress as well as examine the benefits of certain biomarkers to monitor stress, load and injury/illness occurrence in athletes.

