## Methods and analysis

### Study design

The study is designed as a prospective cohort study. All measurements will be conducted over a single handball season, lasting from July 2022 to June 2023 (a total of 46 weeks), with weekly reporting (table 1) and three to five biomarker sampling timepoints (figure 1). We used the Standard Protocol Items: Recommendations for Interventional Trials (SPIRIT) checklist when writing our report.^37^

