#### Weekly load and stress questionnaire

The teams will weekly report training and competition load for each athlete, while academic (educational activities, including lectures, exams and studying) and work load (a part-time or full-time job besides playing sports) for the past 7 days will be reported by the athletes themselves. Competition load will be reported in minutes for each game played in the past week, while training, academic and workload will be reported in hours. The athletes will additionally report average hours slept per day over the past week and rate their perceived overall stress of that week on the scale 1–10.

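### The one analysis set out with explicit factors, a three-period ANOVA, cannot address the load-variation half of the primary aim, and the methods that could are not tied to any load-change measure

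*Protocol article*

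**What the plan says.** The aims paragraph that closes the Introduction (under Biomarkers), like the abstract, includes in the primary aim "how much of a variation in the athlete’s load leads to an occurrence of an injury/illness".

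The data are collected at a resolution that suits the question. Study design describes a season of "a total of 46 weeks", "with weekly reporting (table 1) and three to five biomarker sampling timepoints". Under Weekly load and stress questionnaire, "The teams will weekly report training and competition load for each athlete", while athletes report their own academic and work load. Table 1 defines these loads as hours or minutes per week.

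Statistical analysis names several methods:

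- a "logistic regression model to properly account for the dependency induced by the repeated observations over time within each subject";
- a repeated-measures ANOVA for the effect on injury/illness occurrence, with "time (preparation period vs competition period vs off-season period) as within factor" and "group (injured/ill vs healthy) as between factor";
- independent t-tests between the groups;
- a further step in which "regression analysis will be used to assess predictive power of individual parameters to identify injury/illness occurrence";
- ROC curves to set cut-off values.

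Only the ANOVA comes with its factors stated. None of the others names load, a change in load, a time window, a lag, or the time unit of the outcome.

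**The concern.** The aim is quantitative and ordered in time: how large a variation in load comes before a health problem. The ANOVA fits it badly in three ways.

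1. **Resolution.** It has three levels per player, so up to 46 weekly records must be reduced to three values.
2. **Direction.** Load becomes the dependent variable and injury status the grouping factor. The model estimates how load differs between groups, not how risk changes with load.
3. **Timing.** Group is fixed per player. The period values of an injured player include weeks after the injury, when load may have changed because of it.

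The t-tests share the second and third faults. The article presents the ANOVA as the study of effects on injury/illness occurrence, so readers would take it as the test of the primary aim, and a null result could be read as evidence that load variation does not matter. Meanwhile the change measure, window and lag remain open across four load types (training, competition, academic, work). A change analysis could then be chosen after the data are seen.

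**Working it through.** **Inputs from the article.** Follow-up is 46 weeks with weekly load and health reports. The ANOVA has 2 groups and 3 periods. The sample size is 134/(1 − 0.10) = 148.9, so 149, which reproduces the stated figure. That size rests on an odds ratio of 1.78 for high versus low academic stress, so it gives no guidance on a load-change effect.

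**What a period value keeps of weekly change.** Let L(t) be load in week t of an n-week period. The sum of weekly changes telescopes, so the mean weekly change is

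(L(n) − L(1))/(n − 1).

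If weeks are independent with SD s, one weekly change has SD s√2 and the period's mean change has SD s√2/(n − 1). The ratio is 1/(n − 1). A period mean of load keeps s²/n of the weekly variance s².

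| Weeks in period (assumed) | SD of mean change ÷ SD of one change | Share of weekly variance kept by the period mean |
|---|---|---|
| 6 | 1/5 = 20% | 1/6 = 17% |
| 15 | 1/14 = 7% | 1/15 = 7% |
| 30 | 1/29 = 3% | 1/30 = 3% |

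Three period levels therefore carry very little about week-to-week variation.

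**Simulation 1.** The article gives no event rate or load variance, so every input except 149 players and 46 weeks is assumed: periods of 15, 16 and 15 weeks; independent weekly load around a player mean; odds ratio 1.5 per SD of week-to-week change (signed or absolute); baseline weekly risk 1% or 3%; 300 runs per setting.

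| Risk follows | Weekly risk | ANOVA, group | ANOVA, group × period | Weekly repeated-observation logistic |
|---|---|---|---|---|
| Signed change | 1% | 3.0% | 3.3% | 95.3% |
| Absolute change | 1% | 3.3% | 6.7% | 97.0% |
| Signed change | 3% | 5.3% | 5.0% | 100% |
| Absolute change | 3% | 7.0% | 3.3% | 100% |

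The Monte Carlo standard error at 5% is √(0.05 × 0.95/300) = 1.3 percentage points. All the ANOVA rates lie within two standard errors of 5% (2.5% to 7.5%): no visible power above alpha.

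**Simulation 2.** Here next-week odds rise by 1.3 to 1.5 per SD of the week's load relative to the previous four weeks. Week-to-week variation is 30% and baseline risk 1-3%. Comparing period-mean load between injured and healthy players rejects in 3-5% of runs. A weekly model on the change variable rejects in 62-100%. A weekly model on plain absolute hours, with the same one-week lag, rejects in 46-99.5%, 38-98% and 23-93% of runs when the assumed between-player coefficient of variation is 10%, 20% and 30%.

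So most of the loss comes from moving from weeks to periods. Using absolute amounts costs further power, and it gives a cut-off in hours rather than in size of change.

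**The case against.** The strongest counter-argument is that Statistical analysis opens its modelling with a logistic regression for repeated observations within each subject. With weekly outcomes and loads, that is naturally a player-week model, the very class that performs well above. This stands. A reader might infer that the study cannot answer its aim, or would report no load effect. The article does not support that: such a conclusion holds for the ANOVA and t-tests only, and even absolute weekly hours can detect a change-driven effect.

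Three further points stand in part.

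- The article never says that weekly loads will be averaged. That is inferred from fitting weekly records into three levels. The ANOVA is worded for all dependent variables, and its levels match the training-cycle periods used for blood sampling, where it fits more naturally. No load-specific alternative is given, though.
- The aims paragraph also asks how much overall load an athlete can withstand, for which an absolute cut-off would be relevant. The aim's wording still speaks of variation, and the Introduction (Athlete's stressors) is motivated by increases in training load.
- An article may leave derived variables to a fuller plan. The absence of a change definition alone would not be a finding. The finding is that the analysis actually set out does not match the aim.

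One might also infer that starting in July without earlier load history loses the year's largest rise. The article has no figure for this, so it forms no part of the point.

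**Conclusion.** The point holds in limited form. The three-period ANOVA and the t-tests cannot address the load-variation part of the primary aim. Under the assumed inputs they reject at 3-7%, against 62-100% for weekly models of load change. The logistic and ROC analyses can address the aim, but nothing in the article ties them to a load change.

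The mismatch of resolution, direction and timing follows from the stated factors. The sizes do not: they rest on assumed event rates, effect sizes, period lengths and independent weekly variation, and on an effect that acts only through change. If risk also depended on a player's sustained load, the period comparison would have some power, but for a different question. This is worth correcting before analysis. It does not undermine the data collection.

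**What to change.** State in Statistical analysis that the load-variation aim is analysed with the repeated-observation logistic model already planned, at player-week level.

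- **Exposure:** a pre-specified within-player load change in the week or weeks before the event, for example the week's load minus the player's own mean over a fixed number of preceding weeks. Fix the window and lag for each load type before the data are examined. The lag matters because load and health problems are both reported for the past 7 days, so same-week load can include days after the onset.
- **Scale:** use a difference, not a ratio, for loads that can be zero (academic, work, competition). A ratio is undefined when the reference mean is zero.
- **Between-player term:** include each player's mean load separately, so that change is not confused with who generally carries more load.
- **Cut-offs:** derive the ROC cut-offs on the same change variable.
- **ANOVA and t-tests:** keep them as descriptive for load.

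The cost is revised wording and derived variables from data already collected. The first few weeks serve only as reference. A baseline question on load before July could shorten that loss but is optional.

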## Introduction

Regular moderate exercise is known to have positive health benefits^1^; from preventing a number of non-communicable diseases to improving cardiorespiratory fitness and consequently decreasing cardiovascular morbidity and mortality.^1–3^ Top-level sports, on the other hand, are associated with an increased risk of illness and injury.^4 5^ There has been a number of studies^6–12^ showing a high prevalence of health issues that include injuries and illnesses among elite athletes, ranging from 20% in athletes of all ages^4^ to 45% in youth athletes.^5^ The injuries and illnesses are not only limiting athletes for the time being^13^ but also represent a major burden for sport clubs, health and insurance system and can as well be the reason for sports’ career termination.^14–18^

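### The ANOVA tests of group and group-by-time pool variance over injured/ill and healthy players, so their 5% level is not assured if group sizes and spreads both differ

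*Protocol article*

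**What the plan says.** The Statistical analysis section plans a repeated-measures ANOVA with period (preparation, competition, off-season) as the within-player factor and "group (injured/ill vs healthy) as between factor". Significant group, time or interaction effects lead to pairwise comparisons. A two-group test is added: "For comparison of the groups, we will use independent t-test". The decision rule is "Hypotheses will be accepted or rejected at p≤0.05".

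The one distributional check named is Shapiro-Wilk, and the one fallback is non-parametric statistics when normality fails. Equality of variance is not mentioned, and the t-test is not said to be the pooled or the unequal-variance form.

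The article gives no expected number of injured/ill or healthy players, no SD by group, and no rule for when a player counts as injured/ill. The nearest figure is in the Introduction, where the prevalence of health problems in earlier studies is put at "ranging from 20% in athletes of all ages" up to 45% in youth athletes.

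**The concern.** In a classical repeated-measures ANOVA with two groups, the group F-test is the pooled-variance t-test on each player's mean over periods, and the group-by-time test pools the within-player covariance of both groups. Pooling is harmless when the groups have the same variance, and nearly so when they are of similar size. It fails when both differ: if the smaller group is the more variable, the test rejects too often; if the larger group is, too seldom.

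In a randomised trial the allocation ratio would protect against this. Here the groups are formed by the outcome, so nothing in the design keeps them balanced. Unequal spread is also conceivable for some measures: if injured players miss training and matches, their load averages mix full and missed weeks, which would tend to widen their spread. Shapiro-Wilk concerns the shape of a distribution. Two normal groups with different SDs pass it and go forward to the pooled test.

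At stake is whether a p-value at or below 0.05 from these tests means what the plan takes it to mean. False load differences could be declared, or real ones missed.

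**Working it through.** **The plan's own figures.** The article states no error rate for these tests beyond the nominal 5%. The sample size that sets the number of players reads "with power of 0.90 and α=0.05, two-tailed, which calculated an initial sample size of 134 participants", for "OR=1.78; effect size (ES)=0.14". The dropout step reproduces exactly: 134/(1 − 0.10) = 148.9, hence 149. The 134 is reproduced to within 2 (136) by a within-subject repeated-measures ANOVA with f = 0.14, two measurements and correlation 0.5. Those settings are assumed, because the article does not name the test.

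**Group sizes (assumed).**
- If the cited prevalences were the injured/ill share of 134 players: 20% gives 27 injured/ill and 107 healthy; 45% gives 60 and 74.
- If the group were ever against never affected over the 46 weeks, at a constant weekly rate r of new problems, the healthy share is (1 − r)^46: 0.63 at 1%, 0.39 at 2%, 0.246 at 3%, 0.094 at 5%. Of 149 players that is about 94, 59, 37 and 14 healthy.

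**SD ratio (assumed).** k = SD of injured/ill divided by SD of healthy, from 0.5 to 2.

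**Formula.** With healthy SD = 1, n_h healthy, n_i injured/ill and N = n_h + n_i, in large samples:
- V_pooled = [(n_h + n_i·k²)/N]·(1/n_h + 1/n_i)
- V_true = 1/n_h + k²/n_i
- true two-sided error = 2·[1 − Φ(1.96·√(V_pooled/V_true))]

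**Worked case, 107 healthy and 27 injured/ill.**
- k = 2: V_pooled = (215/134)(0.04638) = 0.0744; V_true = 0.1575; 1.96·√0.4725 = 1.347; error 17.8%.
- k = 0.5: V_pooled = (113.75/134)(0.04638) = 0.0394; V_true = 0.0186; 1.96·√2.116 = 2.851; error 0.4%.
- k = 1: V_pooled = V_true; error 5%. This holds at every split.

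**Worked case, 15 healthy and 134 injured/ill.**
- k = 2: V_pooled = 0.2741; V_true = 0.0965; error 0.1%.
- k = 0.5: V_pooled = 0.0241; V_true = 0.0685; error 24%.

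**Range over k = 0.5 to 2.** Simulation agrees with the formula for the group test and supplies the group-by-time figures:

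| Healthy / injured-ill | Group test | Group-by-time test | Too liberal when |
|---|---|---|---|
| 74 / 60 | 3.8–6.8% | not far from 5% (7.1% at k = 2) | injured/ill more variable |
| 107 / 27 | 0.4–18% | 0.2–25% | injured/ill more variable |
| 37 / 112 | 0.8–15% | 0.5–20% | injured/ill less variable |
| 15 / 134 | 0.1–24% | 0.03–35% | injured/ill less variable |

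Milder ratios do less harm. At 27 injured/ill against 107, the group error is 7.9% for k = 1.2 and 12.4% for k = 1.5.

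**Power.** For a true difference of 0.8 healthy-group SD at 15 and 134, pooled against Welch power is 53% against 76% at k = 1.5 and 23% against 70% at k = 2. At 30 and 119 it is 84% against 93% and 59% against 87%.

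**After the fix.** An unequal-variance test, on raw values or on player means, kept the simulated error at 4.8–5.4% over injured/ill shares of 5–90% and k from 0.5 to 2, with 134 or 200 players. This check covers the group comparison. The replacement for the group-by-time test was not simulated.

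**The case against.** The strongest reply is that the problem needs two conditions, unequal sizes and unequal spreads, and the article establishes neither. That is right, and it limits the point. Three stronger readings are tempting and fail.

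- **That the groups will be very unequal.** This needs an ever-against-never rule and a weekly rate of perhaps 3–5%, neither of which is in the article. At 1–2% per week the healthy share is 63–39%, and at the 45% prevalence the error barely moves. One may reply that a prevalence at one time understates the share affected over a season, but that too leaves the split unknown.
- **That missed effects are the more likely harm.** This holds only if the injured/ill group is both larger and more variable. If it is the smaller group, as at 20%, the same wider spread inflates the error instead. The mechanism of missed weeks also bears on training and competition load only; it gives no reason to expect unequal spread in cortisol, free testosterone, Ig-A, sleep or academic load.
- **That the t-test assumes a common variance.** The article does not say so. The form of the t-test is a detail that an article commonly leaves to the full plan, so this part is a clarification only.

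It is also fair that the section plans logistic regression, further regression and ROC analysis, none of which rests on a common group variance, and that the simulations do not cover the non-parametric path. Nor does correcting the variance settle whether loads averaged over weeks lost to injury are the right contrast; that is a separate question. What stands is that pooling belongs to the ANOVA as named, that group sizes are left to the outcome, and that the named check cannot reveal the problem.

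**Conclusion.** The point holds in conditional form and mainly for the ANOVA. The group and group-by-time F-tests keep their 5% level only if the two groups have similar variance or, approximately, similar size. The design secures neither. Over SD ratios of 0.5 to 2, the departure runs from minor in near-equal groups to a group-test error between 0.1% and 24% at the most uneven split examined; 15 against 134 is an extreme and should not be taken as the expected case. The group-by-time test is the more sensitive of the two. All splits and ratios are assumptions, and the direction cannot be stated in advance. The case for acting is that the exposure is real, the planned check misses it, and the remedy is almost free.

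**What to change.** 1. For group and group-by-time, replace the pooled ANOVA F-tests with a mixed model that has a separate residual covariance for each group, or use heteroscedasticity-robust standard errors. Settle the exact specification, including its small-sample degrees of freedom, when the model is written down, since one group may be small.
2. State that the injured/ill against healthy t-test is read from the unequal-variance (Welch) line, which SPSS already prints.
3. Do not choose between pooled and unequal-variance versions by a preliminary variance test.
4. State the rule that assigns a player to the injured/ill or healthy group, since it determines the split.

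Cost: wording and a different model statement, with no further data. If the variances are in fact equal there is a small loss of power, about 80% against 83% at 15 and 134, and a negligible one in more balanced groups (97% for both at 30 and 119).
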